### Sample size calculations

Victorian Government Department of Education summary statistics compiled in 2023 indicate that, in the 21 regional and remote LGAs of the Southwestern Department of Education region (excluding schools on the geographical fringe of Melbourne in Brimbank, Melton, and Western Melbourne education areas), there were 57,828 children in primary schools. A total of 47,087 (81.4%) children attended the 147 eligible schools with an average of 320 students per school. By recruiting 28 schools and accounting for a 20% school dropout rate, it is anticipated that data will be collected across all time points (baseline, year 1, year 2 and year 3) in 22 schools. A sample of 22 schools, with approximately 200 participating students per school, will provide 83% power to detect a difference of 0.13 units in the primary outcome (z-BMI) between study groups; assuming z-BMI standard deviation 1.1 and intra-cluster correlation coefficient 0.02, as found in the WHO STOPS trial in a comparable population [22,70]. An effect size of 0.13 units in z-BMI it was shown to be achievable, using similar intervention methods, after 2 years in the WHO STOPS trial. Power was estimated using Shiny CRT calculator based on a cluster randomised parallel design with baseline measure, cross-sectional samples, and exchangeable correlation structure (α = 0.05) [71].

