### Randomisation and blinding procedure

After the full sample of schools is recruited schools will be randomly allocated (1:1), to intervention or control groups within strata defined by size (student enrolment ≥120). The study statistician will produce the random sequences and allocation will occur simultaneously for all schools. Given the nature of the intervention, it will be impossible to conceal the allocation from the school communities. However, data analysts will be blind to intervention allocation by removing school identification data.

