### Statistical analysis

Students will be the unit of observation for effectiveness analyses and analyses will be conducted under the intention-to-treat principle. The effect of the STAIR intervention on the z-BMI will be assessed using a linear mixed model with study group, time (baseline, year 1, year 2, year 3), and the interaction group × time as fixed effects. School and student will be included as random effects to account for clustering of students within schools and repeated measures in students measured more than once). Secondary outcomes will be analysed by fitting a generalised linear mixed model with link and distribution selected according to the outcome distribution. Whether age modifies the intervention effect will be explored using the same modelling approach including additional interaction terms. The environmental audit, and implementation outcomes will be analysed at the school level using descriptive statistics and thematic analyses.

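### The 83% power matches a model with equal baseline means, not the planned group + time + group × time model, and it omits repeat-measured children and drift in school means

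*Protocol article*

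**What the plan says.** The protocol article's section "Sample size calculations" would need no comment if it stood alone, so the relevant statements are set out together.

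- **Power, Sample size calculations.** The plan counts on 22 schools with roughly 200 students measured in each, which it says "will provide 83% power to detect a difference of 0.13 units in the primary outcome (z-BMI) between study groups". The z-BMI inputs are an SD of 1.1 and an ICC of 0.02. The calculator was set to a "cluster randomised parallel design with baseline measure, cross-sectional samples, and exchangeable correlation structure", with α of 0.05. The text does not say whether the baseline means of the two arms were held equal.
- **Model, Statistical analysis.** A linear mixed model "with study group, time (baseline, year 1, year 2, year 3), and the interaction group × time as fixed effects", with random effects for school and for student. The student effect is there because some students contribute more than one measurement.
- **Outcome, Primary intervention effectiveness outcomes.** The target is the contrast between arms in how mean z-BMI moves from baseline to year 3. Baseline is measured before the first group model building workshop.
- **Who is measured, Children.** Whoever is present and has not opted out is measured at each of four surveys, so part of the sample recurs.

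**The concern.** A power figure should describe the analysis that will be run. A model with a group main effect, time and their interaction estimates the baseline difference between arms from the data. Where randomisation precedes nothing that could disturb the baseline survey, that difference is zero in expectation, and estimating it costs precision. A calculation that assumes equal baseline means therefore quotes more power than the planned model has on the same inputs.

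Two further simplifications matter. Cross-sectional sampling treats every child as new at each survey, although the model carries a student effect. An exchangeable structure makes a school's underlying mean perfectly stable over three years (CAC of 1). At stake are a headline figure that no planned analysis corresponds to, and some precision that a baseline survey in every school has already paid for.

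**Working it through.** **Inputs.** 22 schools, 11 per arm ("schools will be randomly allocated (1:1), to intervention or control groups"); m = 200, read as students per school per survey; SD 1.1, so σ² = 1.21; ICC 0.02; difference 0.13; α 0.05, taken as two-sided. Power = Φ(0.13/SE − 1.96).

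**Reproducing 83%: common baseline mean, CAC 1, no repeat children.**
- Variance of a school's survey mean: v = 1.21/200 × (1 + 199 × 0.02) = 0.03013.
- Correlation of a school's two survey means: r = 200 × 0.02/4.98 = 0.803.
- Var = (2/11) × v × (1 − r²) = 0.001944; SE 0.0441; z = 2.95; power **83.9%**.

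**Planned model, year-3 contrast, same inputs.**
- Var = (2/11) × 2v(1 − r) = 0.002156; SE 0.0464; z = 2.80; power **79.9%**.
- The gap is 3.9 points. With t on 20 df the two figures are 80.1% and 75.9%.
- Variance ratio, constrained to free: (1 + r)/2 = 0.90.
- With a free baseline, m = 210 gives 81.8% and m = 217 gives 83.1%.

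**Drift in school means, no repeat children.** Here r = 0.803 × CAC. Values of CAC below 1 are assumptions.

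| CAC | Common baseline | Free baseline | Variance ratio |
|---|---|---|---|
| 1 | 83.9% | 79.9% | 0.90 |
| 0.95 | 78% | 72% | 0.88 |
| 0.90 | 72% | 66% | 0.86 |
| 0.80 | 63% | 55% | 0.82 |

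These figures suppose that the standard error reflects the drift.

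**Repeat children.** Grades 1–3 at baseline are grades 4–6 at year 3, so with equal grades at most 100 of 200 can be in both surveys. Let n of them be followed, with within-child correlation π = 0.8 given school (assumed). Using the baseline and year-3 surveys only:

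Var(free) = (2/11) × 2 × {1.21 × 0.98/[200 − n + n/(1 − π)] + 1.21 × 0.02 × (1 − CAC)}

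- n = 5, CAC 1: the bracket is 195 + 25 = 220; Var 0.001960; power 83.6%.
- n = 25, CAC 1: the bracket is 175 + 125 = 300; Var 0.001437; SE 0.0379; power 93%.
- n = 25, CAC 0.9: Var 0.002317; power 77%.
- n = 25, CAC 0.8: Var 0.003197; power 63%.

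For the constrained model, Var = (2/11)(v − c²/v), where v and c are the variance and covariance of a school's two estimated survey means. For n = 25 and CAC 1:
- 175 + 25/1.8 = 188.9.
- v = 0.0242 + 0.5929 × (1/188.9 + 1/300) = 0.02932.
- c = 0.0242 + 0.5929 × (1/188.9 − 1/300) = 0.02536.
- Var 0.00134; power 94%; variance ratio 0.93.

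Multiplying the 0.0242 in c by the CAC gives 82% at CAC 0.9 and 70% at CAC 0.8.

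A cruder calculation on school means alone scales the free variance by 1 − π × n/200. For n = 25 and π from 0.70 to 0.85 it gives 83.4% to 84.2%. Both approaches put the free model above 83% at CAC 1.

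**The case against.** The strongest reply is that the planned model is not the disjoint cross-section model behind 79.9%. It has a student random effect, and some children will be measured repeatedly. At CAC 1, a handful of followed children per school already lifts the free-baseline model past 83%. This stands. A reader might infer that the planned analysis has about 80% power, or that the figure should be reprinted as 80%. The documents support neither, because 79.9% ignores a term in the same protocol's model. But the reply holds at CAC 1. With a quarter of trackable children followed, power is 77% at CAC 0.9 and 63% at CAC 0.8.

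Other points that stand:
- The cluster size is approximate, and about 217 students per school would give 83% with a free baseline. The common baseline in the calculator is an inference from the match.
- A reader might take the baseline constraint to be costless. Equal baseline means require that measurement and opt-out are unaffected by allocation. The text places the baseline survey only before the first workshop, and allocation cannot be concealed from school communities. If the survey follows allocation, the constraint could bias the estimate.
- The planned model does estimate the stated outcome, so the constraint is a gain in efficiency and does not repair an invalid analysis.
- No CAC below 1 appears in the protocol, so the range is an assumption.

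One reply fails: that this is detail an article may leave to the analysis plan. The article prints both a power figure and a model, and the two do not correspond.

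**Conclusion.** The point holds in a limited form. On the stated inputs, 83% to 84% belongs to a model with a common baseline mean, and the planned fixed effects give about 80%. That mismatch is worth about 4 points by the normal approximation.

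The true power of the planned analysis cannot be fixed from the document. It depends on how many children recur, which raises it, and on how stable school means are over three years, which lowers it. Under the assumptions shown, the free-baseline model ranges from 55% (CAC 0.8, no repeat children) to 93% (CAC 1, a quarter of trackable children followed). The documents do not support calling the trial underpowered.

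Dropping the baseline group term raised power in every scenario computed. The variance falls by about 10% at CAC 1 and 18% at CAC 0.8 without repeat children, and by less with them (7% at CAC 1 with a quarter followed). The change is worth making, but the design does not depend on it.

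**What to change.** 1. Confirm that baseline measurement and opt-out precede allocation or are unaffected by it, and say so in the text.
2. If so, make the primary model a constrained one: time, plus group × time at years 1 to 3, with no group term at baseline. Keep the random effects and keep the year-3 contrast as the primary estimate. Report the planned unconstrained model as a sensitivity analysis. If the condition fails, keep the unconstrained model as primary.
3. Restate power for whichever model is used, over a stated range of CAC (for example 0.8 to 1) and of the expected share of children measured more than once. Give the within-child correlation assumed and say whether baseline means were held equal. Do not substitute a single figure of 80%.

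The cost is a change of model wording and a re-run of the calculation. The article reports that recruitment and data collection had not begun. The sponsor must accept that the quoted power becomes a range, which may include values less favourable than 83%.

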### Statistical analysis

Students will be the unit of observation for effectiveness analyses and analyses will be conducted under the intention-to-treat principle. The effect of the STAIR intervention on the z-BMI will be assessed using a linear mixed model with study group, time (baseline, year 1, year 2, year 3), and the interaction group × time as fixed effects. School and student will be included as random effects to account for clustering of students within schools and repeated measures in students measured more than once). Secondary outcomes will be analysed by fitting a generalised linear mixed model with link and distribution selected according to the outcome distribution. Whether age modifies the intervention effect will be explored using the same modelling approach including additional interaction terms. The environmental audit, and implementation outcomes will be analysed at the school level using descriptive statistics and thematic analyses.

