### Children

The research team will visit all participating schools to give a brief presentation about the study to students in grades 1–6 (ages 6–12). They will distribute a plain language statement and an opt-out form for students to take home to their parents/guardians. Students will be included in data collection unless they or their parent/guardian actively opt-out. Surveys will be conducted at the start (baseline), and after the first, second, and third years of the intervention. All children present on the day of data collection who have not opted out will be eligible. Consequently, the composition of children included in each time point of data collection will vary, with some children being followed longitudinally, while others will not.

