### Outcomes

#### Primary intervention effectiveness outcomes.

The primary measure of intervention effectiveness will be the between-group difference in change over time from baseline to year 3 in childhood z-BMI score in repeat cross-sections of grade 1–6 children in intervention and control schools. Cross-sections will be used because we are measuring the effectiveness of the intervention on the school population and not on individual children. Anthropometric data will be collected at each school by trained members of the research team at baseline (pre GMB1), and after 1, 2 and 3 years (primary endpoint). Height (cm) will be measured using a Charder HM-200P stadiometer and weight (kg) using A&D UC-321 digital scales and BMI (kg/m^2^) will be calculated and compared to the WHO reference population [45].

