#### Secondary intervention effectiveness outcomes.

Secondary outcomes include overweight/obesity prevalence of grade 1–6 children, captured at the same four time points, and health behaviours of children in grades 4–6 collected via a self-completed questionnaire on electronic tablets [Samsung Galaxy A9+]. Questionnaires will be completed by classes of children in one school period (~ 45 minutes). The questionnaire will ask about physical activity (self-reported time in moderate to vigorous physical activity, use of active transport to and from school), sedentary behaviour (self-reported screen time for entertainment), diet (intake of vegetables, fruit, water, takeaway foods, sweet snacks, savoury snack and sugar-sweetened beverages), oral health (brushing frequency, oral health, dental care access), sleep (self-reported usual sleep and wake times) and HRQoL (global, physical and psychosocial domains) using validated tools (Table 3) [22,25]. Demographic data will include age, gender, country of birth, and ethnicity. The Index of Community Socio-Educational Advantage (ICSEA) [46] will be used to describe children’s socioeconomic position.

**Table 3 pone.0325853.t003:** Primary and secondary outcomes of interests and proposed instrument/measure in supplementary.

Item	Outcome(s) of interest	Proposed Instrument/measure
**Anthropometry** **(objective)**	• Change in z-BMI score (Primary outcome 1) • Change in overweight and obesity prevalence [47]	Height and weight.
**Physical activity and Sedentary behaviour** **(student self-report)**	• Change in the proportion of participants meeting the Australian 24-Hour Movement Guidelines for Children and Young People (5–17) [48] • Change in the percentage of students taking active transport to and/or from school.	Questionnaire containing modified items from the Core Indicators and Measures of Youth Health [49] and SHAPES [50] surveys.

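### The primary z-BMI model omits age and sex although both are collected and the children measured change at each wave; adding them would bring a small gain at almost no cost

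*Protocol article*

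**What the plan says.** The primary outcome is the "between-group difference in change over time from baseline to year 3 in childhood z-BMI score in repeat cross-sections of grade 1–6 children" (Primary intervention effectiveness outcomes), with BMI scored against the WHO reference. The Statistical analysis section gives the model as a "linear mixed model with study group, time (baseline, year 1, year 2, year 3), and the interaction group × time as fixed effects". It adds that "School and student will be included as random effects to account for clustering of students within schools" and for repeated measures on the same child. No covariate is named.

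Age appears in the analysis in one place only: "Whether age modifies the intervention effect will be explored using the same modelling approach including additional interaction terms". That is an exploratory effect-modification question, not adjustment of the main comparison.

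The section on children says that "the composition of children included in each time point of data collection will vary". The secondary outcomes section says "Demographic data will include age, gender, country of birth, and ethnicity", and that ICSEA "will be used to describe children’s socioeconomic position".

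**The concern.** Each wave is a fresh cross-section of grades 1–6, so the contrast compares four partly different samples per arm. Randomisation balances schools at the start. It does not govern which children are measured three years later in schools that know their allocation.

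The protocol describes several routes by which the measured sample could change:
- Parents or children can opt out, and only children present on the day are measured (Children).
- Each measurement is voluntary, and staff or teachers may have a child skip height or weight (Safety considerations).
- A fifth of schools are expected to drop out (Sample size calculations).

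If these routes work differently by age or sex in the two arms, the shift enters the group × time contrast. Age and sex may also explain some outcome variance that the model now leaves in the residual. The stakes are a little precision and some protection against such shifts, not the validity of the trial.

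**Working it through.** **Inputs.** From Sample size calculations: 22 schools, about 200 students per school, SD 1.1, ICC 0.02, difference 0.13, α = 0.05 (taken as two-sided), cross-sectional samples, parallel design with baseline, exchangeable correlation. With 1:1 allocation there are 11 schools per arm.

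**Variance components.** Total variance is 1.1² = 1.21.
- Between schools: τ² = 0.02 × 1.21 = 0.0242.
- Within schools: σ² = 0.98 × 1.21 = 1.1858.
- Sampling variance of one school's mean at one wave: e = 1.1858 / 200 = 0.005929.

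**Reproducing the stated 83%.** This figure matches a model with no baseline group difference, in which baseline acts like a covariate.
- Variance of a follow-up school mean given its baseline mean: (τ² + e) − τ⁴/(τ² + e) = 0.030129 − 0.000586/0.030129 = 0.01069.
- SE = √(2/11 × 0.01069) = 0.0441.
- Power = Φ(0.13/0.0441 − 1.96) = 83.9%.

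**The contrast the analysis section specifies.** With a free group term plus group × time, the estimate is a difference in change and τ² cancels.
- SE = √(2/11 × 2e) = √(4/11 × 0.005929) = 0.0464.
- Power = Φ(0.13/0.0464 − 1.96) = 79.9%.

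Under exchangeable correlation the result is the same with two or four waves for the baseline-to-year-3 contrast.

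**Adding age and sex.** If they explain a share R² of within-school variance, e becomes e(1 − R²). The documents give no R², so a range is assumed:

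| Assumed R² | SE, group × time | Power, group × time | Power, sample-size model |
|---|---|---|---|
| 0 | 0.0464 | 79.9% | 83.9% |
| 1% | 0.0462 | 80.3% | 84.2% |
| 2% | 0.0460 | 80.7% | 84.5% |
| 5% | 0.0453 | 81.9% | 85.5% |
| 10% | 0.0440 | 83.9% | 87.2% |

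Because z-BMI is already scored against a reference population, 2–5% is a more reasonable working range than 10%. The gain for the specified contrast is then 0.8 to 2.0 points of power.

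**Adding ICSEA.** Suppose it explains 25% or 50% of τ² (assumed). Because τ² does not enter the change contrast, power stays at 79.9%. The sample-size model would give 84.8% or 86.5%, but that is not the model in the analysis section. If three baseline-only schools per arm are kept (28 recruited, 22 complete), power for the change contrast moves from 80.8% to 81.0% or 81.3%. That is negligible.

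**Size of a compositional shift (all inputs assumed).** The bias is the difference between arms in the change in mean age, times the residual z-BMI slope on age.
- 0.1 year × 0.03 per year = 0.003, about 2% of 0.13.
- 0.3 year × 0.10 per year = 0.03, about 23% of 0.13.
- For sex, a 2–5 percentage-point differential shift at a 0.1–0.2 unit sex difference gives 0.002–0.01.

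**How extreme is 0.3 year?** Assume ages uniform over 6–12 (SD 1.73) and simple sampling of 2,200 children per arm per wave. The chance SE of the difference in mean-age change is then 1.73 × √(4/2200) ≈ 0.07 year, so 0.3 year is about four such SEs. Variation in grade mix between schools would raise the SE.

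**The case against.** The strongest defence has four parts.

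**The article may be condensed.** Covariate lists often sit in a SAP, and none is shown. This carries weight. However, the section does not leave the model open: it names the fixed effects and gives age a different, exploratory role. The point is a change to a stated model, not a request for missing detail.

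**z-BMI is already standardised.** This stands in large part. Adjustment can remove only residual age and sex gradients, which is why the gain is small. The documents give no figure for how z-BMI varies with age in this population.

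**Differential drift is not shown.** The protocol says that the children vary between waves, not that the arms diverge. The same grades are surveyed each time, and chance imbalance is already reflected in the standard error. A reader might take the 23% above as the likely bias. The documents do not support that, because it multiplies two assumed extremes.

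**ICSEA and the secondary models.** A reader might infer that leaving out ICSEA also costs precision or protection. For the primary contrast it does not: its stable part cancels, and a school-level index cannot correct for which children within a school are measured. Nor can the secondary models be called unadjusted, since the section gives no fixed effects for them and leaves link and distribution to be chosen.

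**Conclusion.** The point holds as a modest improvement. As written, the primary model has no covariates, although age and gender are collected and the measured children change between waves. The unadjusted analysis is valid.

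Adjusting for age and sex would raise power for the specified contrast from 79.9% to about 80.7–81.9%. That rests on the protocol's planning values, independent cross-sections, exchangeable correlation, a normal approximation and an assumed R² of 2–5%. Adjustment would also reduce bias from differential age or sex shifts. That bias is probably a few thousandths to about a hundredth of a z-BMI unit unless the shift is extreme. It would not touch shifts in unmeasured characteristics.

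The case for naming the same covariates in the child-level secondary models is at least as good, because quality of life, sleep, diet and activity measures are mostly not age- or sex-standardised. No size can be put on it from the documents, and the questionnaire outcomes cover only grades 4–6.

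**What to change.** Amend the Statistical analysis section so that the primary z-BMI model includes age at measurement and sex as fixed effects alongside group, time and group × time. State that the child-level secondary models carry the same two covariates, and report the model without them as a sensitivity analysis. Make no claim that ICSEA improves the primary contrast.

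The cost is a line or two of wording and no new data. The age and gender statement sits with the grade 4–6 questionnaire, so the text should confirm that both are recorded for grades 1–3; an age- and sex-referenced BMI score would normally need them. Two consequences need a sentence each: a simple rule for children with missing age or sex, and a note that in non-linear mixed models the adjusted effect is conditional on the covariates and so differs in meaning from the unadjusted one. The protocol reports that no data have been collected, so the change can be made before any outcome is seen.

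### The primary z-BMI model has no school-by-time random effect, so if schools within an arm drift apart over 3 years, the standard error of the year-3 effect is too small

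*Protocol article*

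**What the plan says.** The primary effectiveness outcome (Primary intervention effectiveness outcomes) is the "between-group difference in change over time from baseline to year 3 in childhood z-BMI score in repeat cross-sections of grade 1–6 children". The Statistical analysis section fits a linear mixed model "with study group, time (baseline, year 1, year 2, year 3), and the interaction group × time as fixed effects", and adds: "School and student will be included as random effects to account for clustering of students within schools and repeated measures in students". It names no school-by-time term, random school slope or robust variance.

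The section on children explains that the sample is mixed over time: "the composition of children included in each time point of data collection will vary, with some children being followed longitudinally, while others will not".

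The sample size section states: "A sample of 22 schools, with approximately 200 participating students per school, will provide 83% power to detect a difference of 0.13 units", "assuming z-BMI standard deviation 1.1 and intra-cluster correlation coefficient 0.02". It describes the design as having "cross-sectional samples, and exchangeable correlation structure". Under that structure two different children in one school are equally correlated whether measured in the same wave or three years apart.

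**The concern.** With one random intercept per school, the model lets a school's mean move over time only by the amount common to its arm. Any further movement of that particular school is treated as independent noise between children and averaged over about 200 of them. The quantity tested is a change, so the intercept drops out and nothing at school level remains in the standard error.

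The protocol gives reasons to expect schools in the same arm to diverge. Each intervention school designs its own actions (Intervention) and is said to differ from the others in its implementation needs (Implementation outcomes). Control schools keep access to two state programs and possibly to health promotion support (Control), and uptake can differ by school. Table 3 tracks change in each school's policy, food and activity environment.

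At stake are the p-value and confidence interval of the primary z-BMI comparison. The error runs toward a false positive, in a trial whose results are meant to guide policy.

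**Working it through.** **Inputs.** From the sample size section: 22 schools, SD 1.1 (variance 1.21), ICC 0.02, α = 0.05, and about 200 children per school, taken here as per wave. The 1:1 allocation gives 11 schools per arm. Assumed: a two-sided test, and the CAC, which the protocol does not give.

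**Step 1: reproduce the stated power.** For a parallel design with a baseline wave, cross-sectional samples and baseline means taken as equal between arms:

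- Variance = (4/22) × (1.21/200) × (1 + 199 × 0.02) × (1 − r²), with r = 200 × 0.02 × CAC / (1 + 199 × 0.02).
- At CAC = 1: r = 4/4.98 = 0.803, SE = 0.0441, power = Φ(0.13/0.0441 − 1.96) = 83.9%.

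This is within one point of the stated 83%. With a free group effect at baseline, as in the planned model, power at CAC = 1 is 79.9%.

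**Step 2: SE under the planned model, no repeat children.** The school intercept cancels from the change:

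- SE² = (4/11) × 1.21 × 0.98 / 200 = 0.002156, so SE = 0.0464.

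**Step 3: true SE if schools drift.** A school-by-wave component of variance 1.21 × 0.02 × (1 − CAC) enters at both waves:

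- SE² = (4/11) × [1.21 × 0.98 / 200 + 1.21 × 0.02 × (1 − CAC)].
- Type I error = 2Φ(−1.96 × 0.0464 / true SE).

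| CAC (assumed) | Drift SD per school and wave | True SE | True/model SE | Type I error | Power, correct SE, group × time model | Power, correct SE, baseline constrained |
|---|---|---|---|---|---|---|
| 1 | 0 | 0.0464 | 1.00 | 5.0% | 79.9% | 83.9% |
| 0.98 | 0.022 | 0.0483 | 1.04 | 5.9% | 76.8% | 81.3% |
| 0.95 | 0.035 | 0.0510 | 1.10 | 7.4% | 72.3% | 77.6% |
| 0.90 | 0.049 | 0.0551 | 1.19 | 9.9% | 65.5% | 72.0% |
| 0.80 | 0.070 | 0.0626 | 1.35 | 14.6% | 54.7% | 63.0% |

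A simulation of the four-wave random-intercept analysis (2,000 runs per setting) gave type I error of 4.8%, 8.0%, 9.9% and 16.0% at CAC 1, 0.95, 0.90 and 0.80. The average model SE stayed at 0.046 to 0.047, while the actual spread of the estimate rose to between 0.051 and 0.064 once CAC was below 1.

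**Step 4: children measured more than once.** At most half of the grades overlap between baseline and year 3, since grades 1–3 become grades 4–6. The student effect rightly uses these pairs to reduce child-level variance, but school drift is untouched and becomes a larger share of the true variance. Take a four-wave calculation with grade progression, 80% attendance per wave and a within-child correlation of 0.8 (the last two assumed). The model SE falls to 0.025, and type I error is 8%, 13%, 20% and 31% at CAC 0.98, 0.95, 0.90 and 0.80. With a within-child correlation of 0.6 the figures are about 7%, 10%, 14% and 22%.

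**The case against.** The strongest reply is that the inflation is conditional. Under the exchangeable structure that the protocol assumes, the planned model is valid and the error is 5%. No section gives a CAC, and near 1 the harm is small: 5.5% at 0.99 and 5.9% at 0.98 without repeat children. This stands, and it limits what can be claimed.

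Four stronger readings are tempting, and the protocol does not support them:

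- *Type I error does exceed 5%.* This needs CAC below 1, which is plausible here but is not a figure in the document.
- *Pupil turnover proves CAC below 1.* Overlap of children and autocorrelation of the school mean are separate quantities. With no overlap and CAC = 1, a school intercept is correct. Only school-specific drift matters.
- *The test will use degrees of freedom based on thousands of children.* No method is named, and an article may leave it to the analysis plan. The figures above use 1.96 throughout and do not depend on it.
- *Every secondary model has the same fault.* The text says only that generalised linear mixed models will be fitted, with link and distribution to suit the outcome. It does not give their random effects.

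It can also be said that a condensed article does not exclude a school-by-time term in an unseen analysis plan. But the article does specify the random part, gives the purpose of each term, and uses the matching assumption for power. That weakens the point without removing it.

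**Conclusion.** The point holds in conditional form for the primary z-BMI model. As written, the standard error of the baseline-to-year-3 contrast leaves out any school-specific change. The 5% level is kept only if schools within an arm do not diverge at all over three years.

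The mechanism is certain; its size is not. Without repeat children, type I error runs from 5% at CAC 1 to about 15% at CAC 0.80. A drift SD of only 0.049 z-BMI per school and wave (CAC 0.90), small beside the target of 0.13, would double the nominal error. With tracked children the error is higher, but those figures also rest on assumed attendance and within-child correlation and should be read as illustrations.

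The 83% power is not an arithmetic error. It rests on the same assumption of CAC = 1 and falls if that assumption fails.

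**What to change.** - Add a school-by-time random effect to the primary linear mixed model and keep the school and student effects. If its variance is estimated as zero, the random part is the one now planned.
- Test group × time at year 3 with a small-sample degrees-of-freedom correction suited to about 22 schools, such as Kenward-Roger or Satterthwaite.
- If the secondary generalised linear mixed models share the school and student effects, use the same added term there.
- State that the 83% power assumes CAC = 1, and show power over a range below 1, as in the table.

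The cost is one variance term and a degrees-of-freedom option. Confidence intervals widen and power falls if schools do drift. The article reports that no data had been collected, so the change can still be pre-specified.
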